#### Trial outcome measures will be divided into three broad categories

*Decision measures* will include decision self-efficacy [21], decision conflict score [32], decision preference, and decision choice [33]. These three instruments will be given at T0 (baseline) and T1, after the surgical consultation with the plastic surgeon.

1) The decision self-efficacy (DSE) scale is a prospectively designed instrument to evaluate patient self-confidence in decision-making, including shared decision-making [21]. It has been validated among women facing treatment decisions for osteoporosis [21] and used in cancer patients [22]. Psychometric evaluation has shown high levels of internal consistency (Cronbach’s alpha 0.90). Decision self-efficacy is correlated with decision conflict subscales of feeling informed (*r* = 0.47) and supported (*r* = 0.45) [21]. This instrument has never been tested in the breast cancer or breast reconstruction population.

2) The decision conflict scale measures personal perceptions of uncertainty in choosing options and has been demonstrated to be valid and responsive to change [32]. The decisional conflict scale is a 16-item 5-response instrument that reports a score from 0 – 100 with higher scores indicating more conflict (items are summed, divided by 16 and multiplied by 25) [26,34].

3) Decision Preference and Decision Choice has been used as a primary and secondary outcome in studies of decision support interventions in cancer patients. It demonstrates good test-retest reliability (test-retest coefficient > 0.90) and is sensitive to change when measured before and after an intervention [33].

*Patient reported outcomes (PRO)* will be measured using the perceived involvement in care scale [35] (PICS) and satisfaction with information subscale of BREAST-Q [36-39].

1) PICS is a measure of patient perception of involvement with her care, and has seven 5-point Likert scale items that assess the extent to which the patient asked questions, offered opinions, and expressed concerns when meeting with the surgeon [35].

2) The BREAST-Q is a procedure-specific and validated PRO that measures Hr-QOL and patient satisfaction with PMBR [36-39]. The “Satisfaction with Information” Subscale specifically measures patient satisfaction with the preoperative information and care provided by the plastic surgeon and other members of the medical team. There are 15 items that use a four-level Likert scale response format; the score is transformed on a scale of 0 to 100 with higher scores indicating greater satisfaction [36-39].

*Service outcomes* will be measured using the uptake rate of breast reconstruction, consultation length, number of consultations until a decision is made (consent signed), the physician satisfaction scale [40], and a breast reconstruction knowledge test [41].

### Baseline measures

Patient demographic and clinical characteristics, baseline psychosocial measures such as the Spielberger State-Trait Anxiety Inventory (STAI) [42], a social support survey [43], and preference for decision control [44] will be captured on our routine two-page patient intake form after consent but prior to randomization and allocation (T0, Figure 1). Baseline covariates that will be documented include demographic variables, including age, marital status, ethnicity, household annual income, highest level of education, urban vs. nonurban place of residence, and employment status, and clinical covariates, including study site, timing of the reconstruction (immediate vs. delayed), previous stage of breast cancer, prior receipt of radiation, prior receipt of chemotherapy, and presence of chronic illness.

STAI is a 20-item measure of anxiety, and its scores range from 20–80, with a higher score indicating greater anxiety [42]. The STAI trait subscale will be measured at baseline, and the state subscale will be measured at baseline and T1. The state subscale is a sensitive indicator of changes in transitory anxiety in behavior modification programs or with experimental procedures.

The Medical Outcomes Study Social Support Survey has a series of 18 questions that measure four domains of social support (emotional, tangible, affectionate, and social interactions). Responses range from 1 (none of the time) to 5 (all the time). The items in each domain were summed and then transformed to yield scores ranging from 0 to 100. Higher scores indicate more support [43].

Preference for Decision Control is assessed using a validated question from previous studies in cancer patients where patients indicate whether they want to play an active, passive, or collaborative role with their physician when making a treatment decision [35].

### Analysis

Analysis of primary and secondary outcomes from the main trial will be summarized using measures of central tendency and dispersion. This pilot study will provide important information regarding the treatment effect estimate and variability (standard deviation) to supplement what has been reported in observational studies and will be used to guide the design and sample size calculation for the main trial. Because this is a pilot study, we do not propose to undertake formal hypothesis tests of the primary or secondary endpoints for the definitive trial.

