### Pilot study objectives

1. To determine feasibility and acceptability of randomization, intervention uptake, and data collection

2. To assess implementation and fidelity of the outcome measures and intervention

3. To pilot trial procedures including recruitment (giving information and obtaining preliminary consent via telephone recruitment), randomization, intervention delivery (workshop scheduled same day as initial surgical consult), and outcome measurement (mailed questionnaires)

4. To use qualitative research methods to assess the content and acceptability of the intervention and learn from patient interviews how to improve the delivery of the intervention for the full trial

5. To obtain estimates of variance and a preliminary estimate of the effect of the intervention on preliminary trial outcomes (decision self-efficacy, satisfaction with information, decision preference and decision choice, decisional conflict) and service outcomes such as duration of consultation.

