### Participants

Adult women referred to one of the plastic surgeons for consideration of breast reconstruction will be eligible to participate. The study coordinator is responsible for identification and recruitment of potentially eligible participants. Because the intervention (educational workshop) will occur *before* the initial surgical consultation, it is necessary to identify subjects from faxed referrals and determine their eligibility via telephone confirmation at the time of recruitment and prior to the initial surgical consultation. Participants will be excluded if they are referred for reconstruction after atypical breast malignancy (e.g., angiosarcoma) or metastatic breast cancer, secondary breast reconstruction, have cognitive impairment or uncontrolled psychiatric diagnosis, or cannot read or write in English. Once eligibility has been confirmed with the study coordinator, subjects who indicate an interest in participation will be enrolled after providing informed consent over the telephone, and study packages will subsequently be mailed. Participants will be officially registered upon receipt of signed consent through return mail. Baseline measures (T0) will be assessed prior to randomization and returned in postage-paid envelopes. Participants in the study and control groups will complete T1 measures approximately 1 week after the initial surgical consultation. The participant timeline is outlined in Figure 2.

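### The decision measures are taken before randomization and again at T1, but the Analysis section names no use of the T0 score in the effect estimate or in the inputs to the main-trial sample size

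*Protocol article*

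**What the plan says.** All places are in the protocol article.

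- **Timing of the measures.** The trial outcome section lists decision self-efficacy, decisional conflict, and decision preference and choice as decision measures, and states: "These three instruments will be given at T0 (baseline) and T1, after the surgical consultation with the plastic surgeon".
- **T0 precedes allocation.** Under Participants: "Baseline measures (T0) will be assessed prior to randomization and returned in postage-paid envelopes". The randomization section adds that the envelope is opened only once the baseline questionnaire has come back. Both arms then "complete T1 measures approximately 1 week after the initial surgical consultation".
- **Purpose.** Objective 5 is "To obtain estimates of variance and a preliminary estimate of the effect of the intervention on preliminary trial outcomes", and decision self-efficacy and decisional conflict are among the outcomes it lists.
- **Analysis.** Outcomes "will be summarized using measures of central tendency and dispersion". The pilot is to give "important information regarding the treatment effect estimate and variability (standard deviation) to supplement what has been reported in observational studies", and this "will be used to guide the design and sample size calculation for the main trial". Formal hypothesis tests are ruled out.

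The Analysis section does not say whether T1 scores, changes or baseline-adjusted values are summarized, and it mentions neither a residual SD nor a T0-T1 correlation.

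**The concern.** The T0 score precedes randomization, so it is a valid covariate. Item non-response aside, it is available for every randomized woman. For an outcome measured before and after, it is usually the strongest predictor of the T1 score. Three things follow if it is not used.

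1. The preliminary effect estimate, which objective 5 asks for, is less precise than the same data allow.
2. A chance difference between arms at T0 passes into the unadjusted effect in proportion to r. Allocation is balanced in blocks of ten with no stratification described, so nothing in the design limits such a difference.
3. The SD of a single score is enough to size a trial that compares unadjusted T1 means. A trial analysed by ANCOVA or on change scores also needs r. The pilot collects the data for r, but the article does not list it as an output.

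**Working it through.** **Inputs from the article:** about 40 women (Sample size and power), 1:1 allocation, so about 20 per arm; T0 before randomization and T1 after the consultation.

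**Assumptions not in the article:** r = 0.3 to 0.7; equal SD in both arms and at both times; for the main-trial illustration, two-sided alpha 5%, power 80% and a true difference of 0.5 SD.

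**The plan's own figure.** The 40 rests on a cited recommendation for pilot studies, with no alpha, power, effect or SD behind it, so no power formula can reproduce it. It agrees with the stated capacity: 4 clinics × 10 = 40 women, and 4 workshops × 5 = 20 in the workshop arm. No main-trial sample size is given.

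**1. Precision of the pilot effect (in SD units).** The standard error of a difference is √(4/40) = 0.316. With t on 38 df = 2.024, the unadjusted 95% half-width is 2.024 × 0.316 = 0.64. ANCOVA multiplies it by √(1 − r²):

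| r | √(1 − r²) | Half-width |
|---|---|---|
| 0.3 | 0.954 | 0.61 |
| 0.5 | 0.866 | 0.55 |
| 0.7 | 0.714 | 0.46 |

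This ignores the one degree of freedom and the small cost of estimating the slope.

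**2. Chance imbalance.** The T0 difference between arms also has standard error 0.316 SD. A gap of 0.3 SD or more, in either direction, is 0.3/0.316 = 0.95 standard errors and has probability of about 34%. An unadjusted effect is shifted by r × gap, for example 0.5 × 0.3 = 0.15 SD.

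**3. What the SD alone leaves open.** The per-arm number is 2(1.96 + 0.842)²/0.5² = 62.8 on the raw SD, rounded up to 63, or 126 in total. ANCOVA multiplies 62.8 by (1 − r²); a change-score analysis multiplies it by 2(1 − r).

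| r | Raw T1 total | ANCOVA total | Change-score total |
|---|---|---|---|
| 0.3 | 126 | 116 | 176 |
| 0.5 | 126 | 96 | 126 |
| 0.7 | 126 | 66 | 76 |

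Relative to ANCOVA, the raw SD overstates the size by 1/(1 − r²): 1.10, 1.33 and 1.96. A trial sized at 126 and analysed by ANCOVA would have power of about 84%, 90% and 98%. A shortfall arises only for change scores with r below 0.5.

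**4. How well 40 women estimate these inputs.**

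- The 95% CI for an SD on 38 df is 0.82 to 1.29 times the estimate. The sample size scales with its square, so the range is 0.67 to 1.66 times.
- For r = 0.5, Fisher's z gives 0.549 ± 1.96/√37 = 0.549 ± 0.322, so the CI for r is 0.22 to 0.70.
- Sizing on the lower limit gives a factor of 1 − 0.22² = 0.95. The per-arm number is 62.8 × 0.95 = 59.7, rounded up to 60, so the total is 120 instead of 126.
- At an observed r of 0.3 the lower limit is about zero and nothing is saved. At 0.7 it is about 0.50, and the factor is about 0.75, not 0.51.

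**The case against.** The strongest case against is that this argues from silence. A condensed article commonly leaves estimators and covariates to the full protocol or SAP. The Analysis section does not say that the summaries are confined to raw T1 scores. Central tendency and dispersion can be reported for T0, T1 and change, and the T0 data are kept, so r could be computed later.

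A reader might infer two stronger things: that the plan discards the baseline, and that it will mis-size the main trial. The article supports neither. There is no main-trial sample size, formula, target difference or analysis model to be wrong, and the primary outcome is still to be informed by the qualitative work (Interpretation of pilot results). The pilot only guides the calculation, alongside observational data. A raw SD is valid for an unadjusted trial and errs towards more power for an ANCOVA trial.

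Little in the pilot itself turns on the point. No test is planned, so no power is lost, and the success criteria are recruitment, retention, completion and fidelity. The pilot also monitors how many baseline questionnaires are complete, so some T0 scores may be missing.

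All of this stands as a limit on the claim. What remains is that the section is not silent. It states a method and names the SD as the variability input, while objective 5 asks for an effect and a variance on measures whose baseline is already collected.

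**Conclusion.** The point holds as an inexpensive improvement, not as an error that invalidates anything. The firmer gain is in the pilot effect estimate: at an assumed r of 0.5 the 95% half-width falls from about 0.64 to 0.55 SD (to 0.61 at r = 0.3, and to 0.46 at r = 0.7), and dependence on chance baseline imbalance is removed. The second gain is completeness of the planning inputs, because without r the designers cannot size an ANCOVA or change-score trial.

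The apparent excess of 10% to 96% in main-trial size should not be read as a forecast. It uses assumed point values of r. With 40 women and an observed r of 0.5, a lower-limit r saves about 5%, well inside the uncertainty from the SD itself. The conclusion is limited to continuous measures taken at both times, and for sizing it matters only if one of them becomes the primary outcome.

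**What to change.** In the Analysis section, for continuous outcome measures taken at T0 and T1 (at least decision self-efficacy and decisional conflict), add:

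- the between-arm difference estimated by ANCOVA of the T1 score on arm and T0 score, with a 95% CI and no hypothesis test;
- the residual SD, and the T0-T1 correlation with its 95% CI, reported alongside the raw SD;
- a statement that, if such a measure becomes the main-trial primary outcome, these figures will inform its sample size with a conservative value of r, such as the lower confidence limit.

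The cost is a few lines of analysis and one degree of freedom per model. It needs no new data, no extra patient burden and no change to the decision not to test.

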### Qualitative analysis

Thematic analysis [45] will be used to extract emerging themes and variations. Concurrent data collection and analysis will be undertaken using multi-layered reading and constant comparison [46]. N-vivo 10.0 software will be used for data management. An audit trail, detailed field notes, and memos will be maintained throughout the research process.

### Sample size and power

Sample size for the pilot study is determined based on the recommended sample size of approximately 40 participants for a pilot study [47]. Approximately 20 patients are referred for breast reconstruction per surgeon per month. Workshops and clinics have the capacity for five and ten patients per session, respectively. A conservative estimate of 50-70% recruitment would allow us to recruit our pilot sample size over 6 months across four clinics.

### Interpretation of pilot results

Feasibility targets include ≥ 60% recruitment, ≥ 80% retention after randomized treatment assignment, and ≥ 80% completion of primary outcome measure. Success will also be measured based on high treatment fidelity measured through observation of the intervention and participant qualitative report. To inform our decision for the primary outcome for a definitive RCT, the most important outcome measure for patients will be solicited and ascertained through qualitative methods.

## Discussion

To reduce unnecessary variation in treatment and improve quality of cancer care among breast cancer patients, there has been a growing interest in engaging patients through the decision-making process [48,49]. Particularly for breast reconstruction there is a paucity of studies designed to address patients’ unique informational and supportive-care needs, and there has been a call to action to develop and implement interventions that enhance patient empowerment [50]. Only one RCT has designed and implemented a decision support intervention for patients considering breast reconstruction [51]. While patients assigned to the pre-consultation computer-based decision support intervention demonstrated greater knowledge scores, outcomes related to shared decision-making or decision quality were not assessed using validated instruments [51]. Retrospective observational studies from single institutions suggest that well-informed patients already participate in the decision whether or not to undergo breast reconstruction [12,41], but interventions can improve involvement and satisfaction for the decision regarding the type of reconstruction (implant-based or autologous tissue reconstruction) among women who decided to have breast reconstruction [52]. However, inferences regarding the utility of decision-support interventions for breast reconstruction patients from non-randomized and particularly retrospective studies must be made with caution. Furthermore, no study has examined the potential of group workshops to enhance patient engagement and decision quality; educational interventions delivered in a group setting have been demonstrated to be an effective tool to address informational and psychosocial needs for breast cancer survivors [30]. Therefore, we designed a novel intervention to address identified gaps in care to promote shared decision-making and improve the quality of patient decisions surrounding breast reconstruction.

Because the intervention occurs *before* the initial surgical consultation (necessitating telephone recruitment) and is delivered using a *novel format* in a group setting, we felt it would be most appropriate to first undertake a pilot study prior to a definitive trial. Our pilot study seeks to identify (1) the feasibility, acceptability, and design of a definitive RCT and (2) the optimal content and delivery of our proposed educational group intervention. Results from our pilot study will be used in the following two ways: (1) to validate the design of the intervention and revise content and delivery to meet the needs of the end-users; (2) to inform the final design and sample size estimation for a definitive RCT.

## Trial status

The pre-consultation educational group intervention pilot trial began recruitment in January 2013. Thirty patients have been recruited to date (18 May 2013), of whom 15 have been randomized to one of three decision support workshops. Once all participants have been recruited and enrolled, we will complete qualitative interviews among a purposeful sample of voluntary participants. Recruitment is ongoing, and the trial is scheduled to be completed by the end of this academic year (June 2013).
